**Fig. 1 Fig1:**
[figure not shown]
CONSORT diagram

##### Allocation strategy

Randomisation will take place after baseline (T0) data collection has been completed. School is the unit of randomisation. Six schools will be randomly allocated into the intervention arm and six into the control arm, stratified by local authority area (South Gloucestershire:North Somerset at a ratio of 2:1 in each arm) and recruitment method (recruitment method A:B at a ratio of 1:1 in each arm). There is potential that recruitment method B may influence children to increase their physical activity prior to baseline measurements; hence, equal numbers of taster session schools will be allocated to control and intervention arms so that any effects of the taster sessions would be balanced between the two arms and can be separated from intervention effects. Allocation will be performed (computer-generated allocation) by an independent member of the Bristol Randomised Trials Collaboration who will be blind to the school identity.

#### Phase 3: the Action 3:30 intervention and T1 data collection

Each intervention school will receive the Action 3:30 after-school club for a total of 15 weeks. The intervention will run between November and March, when the children are in years 4/5. To minimise the displacement of existing after school provision intervention, schools will be encouraged to run the two weekly sessions whenever it is most convenient to do so in the timetable, providing it takes place straight after school.

To deliver the intervention, two TAs from each intervention school will attend a 25-h (5-day) training programme focussing on delivering a physical activity programme after-school. Action 3:30 is based on principles derived from Self-Determination Theory (SDT) [18, 27], and as such, the programme will focus on promoting children’s perceptions of autonomy, belonging and competence in relation to physical activity. Among a range of techniques to promote autonomy, TAs will be encouraged to provide choice within the activities, such as leading warm-ups and adapting games and in regard to the speed at which activities progress. TAs will be trained to support competence by setting progressive activities targeting quick success balanced by optimal challenge. They will give specific praise for attempts as well as outcomes. Relatedness will be supported through empathetic TA-child interactions. Our previous study showed that TAs are able to deliver Action 3:30 in line with these strategies and the revised version of the TA training aims to clarify misunderstandings and common problems.

The 5-day training programme will be delivered by the Coach Development Manager at Bristol City Council. Once trained, TAs will deliver Action 3:30 twice a week for 15 weeks. Each session will last 60 min. Thirty detailed session plans have been produced and TAs will be asked to deliver sessions in the prescribed order. The session plans include a range of activities and games and emphasise participation and enjoyment. For 22 of the session activities, there is a video recording of model delivery; on 19 session plans, there are links to additional online resources; and on all 30, there are reminders for the TAs on how to embed the core principles of SDT within the session. Pupils will additionally be provided with 10 home activity cards that will be distributed after every three sessions. The cards reinforce session content and provide advice on how children can practice activities that have been taught during the sessions with family and friends.

##### T1 data collection

Follow-up (T1) measures, identical to those conducted at baseline (T0), will be conducted with the same children measured at baseline during the final 3 weeks of the intervention period in each intervention and control school. In those four schools where all children in year 3/4 wore accelerometers in the opt-out consent phase, this will also be repeated at T1 (now year 4/5). Details of how these data will be used are in the “Quantitative analysis” section of this paper.

##### School and pupil appreciation

Intervention schools will receive TA training and £200 worth of equipment to use for the Action 3:30 club. Schools will be remunerated for 2 h each week at an appropriate TA rate to cover the delivery cost. Control schools will receive a £300 donation to the school fund in recognition of their participation. All children who wear accelerometers at the ‘opt-out’ phase and all children who take part in the T0 and T1 measures will receive a small thank-you gift at each time point. The gift will be selected to promote physical activity and encourage prompt return of the accelerometers.

##### Re-enrolment

Data from the original Action 3:30 study and a recent evaluation of an extra-curricular dance programme highlighted that normally schools provide an opportunity for pupils who did not register an interest at the start of an after-school programme to join at a later date [12, 17, 28]. To enhance external validity, we will assess attendance rates in the intervention schools at the end of the first school term (December, 2017). If children have dropped out, we will re-enrol children who consented to the main study but did not get selected and carry out T0 measures with them before the club starts again in the second school term (January 2018). These children will also therefore be measured at T1.

#### Phase 4: process evaluation and economic evaluation

##### Process evaluation

The number of schools approached and proportion recruited will be recorded. After each Action 3:30 intervention session, TAs will be asked to record attendance and dose of the intervention (whether sessions were delivered as planned), using a log book. A member of the project team will observe three randomly-selected sessions in each intervention school to assess whether the core components of the sessions were delivered as planned. TAs will report their self-efficacy to deliver physical activity sessions (including behaviour management) before and after the TA training and after each of the observed sessions. The original scale was developed for physical education teachers [29] and has been adapted to the teaching assistant context.

The intervention participants will be asked to complete a brief perceived enjoyment questionnaire during each of the observation visits. School physical activity context will be assessed during one of the observation visits; school-level physical activity provisions will be measured using a validated school physical activity environment scale [30], and information about school physical activity policy context will be collected via an interview with the key contact, supported by a validated school policy scale [31]. School physical activity context is being measured so that any differences in social/physical environment and school policy strategies which might impact the delivery of an intervention (or how the participants might respond to it) can be examined.

The Coach Development Manager at Bristol City Council will be asked to take part in an interview, focusing on the delivery of the training and whether it could be improved. They will also be asked to complete a checklist to assess whether TA training was delivered as planned.

Following completion of the 15-week Action 3:30 programme, all intervention TAs (*n* = 12) and intervention school contacts (*n* = 6) will be asked to take part in a semi-structured interview, and children (*n* = 6 boys, *n* = 6 girls per intervention school) will be asked to take part in focus groups. The interviews and focus groups will examine factors that may have affected recruitment, attendance, delivery and enjoyment and will ask for opinions on how these elements could be improved. Child focus groups will include questions relating to whether children’s perceptions of autonomy, belonging and competence were supported by the intervention and their interactions with the TAs. TAs will also be asked about the effectiveness of managing disruptive behaviour, their training and whether it could be improved. School contacts (staff members who act as the primary liaison between the school and the study team) will be asked about the long-term sustainability of the Action 3:30 programme and feasibility of the re-enrolment stage.

Interviews will be conducted with school contacts and class teachers in the four schools that took part in the accelerometer opt-out process. The interviews will focus on school burden and how it could be reduced, logistical issues and how the opt-out consent process could impact participation in a future trial.

Interviews (*n* = 8) will be conducted with leaders of school consortium groups, common in the English education system and local public health commissioners to discuss the sustainability and potential future dissemination of the intervention.

##### Economic evaluation

We will ask all 12 schools to report number, cost and funding source of all their extra-curricular clubs, using a retrospective survey at T0. The project team will track the costs and resources used to prepare and deliver Action 3:30. Parental time to collect children after-school by travel mode will be estimated from pupil self-reported data. The economic assessment will be based on the RE-AIM framework [32] and will assess the potential for change in health-related quality of life (*Effectiveness*), the ability to assess costs variation in delivery among school settings (*Implementation*) and the potential to sustain the outcome of the intervention from a cost perspective (*Maintenance*).

### Analysis plan

#### Quantitative analysis

The main analysis will focus on data relating to characteristics of the sample, recruitment, retention and Action 3:30 session attendance rates, levels of data provision using appropriate descriptive statistics (M, SD, Median, N & %). Evidence of promise of the intervention (i.e., estimates of the potential effect of the intervention on weekday MVPA) will be estimated using random-effects linear regression models adjusting for intervention group, local authority, and baseline MVPA with a focus on 95% confidence intervals with exploratory subgroup analyses by child gender. We will also examine the physical activity profile of children who did not attend the Action 3:30 sessions to assess whether their baseline physical activity levels were different to children who attended.

Secondary analysis will pilot the use of a complier average causal effect (CACE) analysis [33] for the four schools that used the “accelerometer opt-out” consent procedure. This model will examine the effect of receiving Action 3:30 on MVPA (original recruits and late joiners) when compared to the control arm and will provide an indication of the overall benefits of the study for all participants who were exposed to Action 3:30 as part of the original sample and late joiners.

Potential sample sizes for a future definitive trial will be estimated using the derived intraclass correlation coefficient (ICC) for MVPA from this study and published ICCs from comparable studies, the target differences in MVPA, and combinations of key parameters (type I and type II error).

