#### Phase 2: baseline (T0)

##### Recruitment

We aim to recruit 30 year 3/4 pupils from each school. As girls are less active than boys [21], we will aim for a minimum of 40% of the sample to be girls. All year 3 and 4 children able to regularly take part in physical education lessons will be eligible. In schools where more than 30 children consent, 30 will be randomly selected for the study.

Two methods will be trialled for phase 2 recruitment: briefing (recruitment method A) or briefing plus taster session (recruitment method B). A goal of this project is to examine which of the two approaches is most effective for recruitment, to inform a recruitment strategy in a definitive future trial. Recruitment method A will involve a short briefing in each class to explain the study and provision of student information sheets and parental study information (information sheet and parental consent form to return). Recruitment method B will involve the briefing plus a taster session. Taster sessions will be led by coaches from Bristol City Council (a collaborating partner) and will involve a 20–30-min activity session like that of the Action 3:30 after-school club. Four schools in South Gloucestershire and two in North Somerset will be randomly selected to receive the taster sessions. Written parental consent will be obtained for all participants [22]. A brief questionnaire will be sent home to parents who do not give consent for the main study to assess the reasons for not wanting their child to take part.

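### The weekday MVPA model adjusts for one randomisation stratifier (local authority) but not the other (recruitment method), so any lasting taster effect would widen the CI and raise a model-based ICC without biasing the intervention estimate

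*Protocol article*

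**What the plan says.** The Allocation strategy section of the protocol article sets equal arms, "Six schools will be randomly allocated into the intervention arm and six into the control arm", and names two stratifiers. The first is "stratified by local authority area (South Gloucestershire:North Somerset at a ratio of 2:1 in each arm"). The second is "and recruitment method (recruitment method A:B at a ratio of 1:1 in each arm"). The Recruitment section fixes the taster schools: "Four schools in South Gloucestershire and two in North Somerset will be randomly selected to receive the taster sessions".

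The Allocation strategy section also says why recruitment method is a stratifier: "There is potential that recruitment method B may influence children to increase their physical activity prior to baseline measurements". Equal allocation of taster schools is meant to ensure that "any effects of the taster sessions would be balanced between the two arms and can be separated from intervention effects".

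The Quantitative analysis section states the model for weekday MVPA as "random-effects linear regression models adjusting for intervention group, local authority, and baseline MVPA", with attention to 95% confidence intervals and exploratory subgroup analyses by gender. It adds that the ICC from this study, together with published ICCs, will inform the sample size of a definitive trial. The fifth progression criterion, given under Qualitative analysis, requires at least a small weekday MVPA benefit for boys and for girls, with an upper 95% bound above 10 min for each.

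**The concern.** The analysis should follow the randomisation. Here it follows one stratifier and drops the other, and the one dropped is the one the protocol itself expects might affect activity. The covariates are an explicit list rather than a reference to stratification factors in general, so the mismatch is stated in the text and is not a detail deferred to an analysis plan.

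Stratifying on a factor removes its variation from the comparison of arms. If the model then ignores that factor, the standard error still counts the variation. Two outputs used for decisions depend on it:

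- **Interval width.** The fifth criterion asks whether the upper bound exceeds 10 min, so a needlessly wide interval works in favour of progression.
- **ICC.** A between-school variance that includes a taster effect gives a larger ICC, and so a larger definitive trial if that ICC is used.

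**Working it through.** The article states no SD, ICC, power or taster effect, so there is no figure of its own to reproduce.

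**1. Is arm separable from method?** Eight South Gloucestershire and four North Somerset schools, with four and two of them given tasters, form cells of 4, 4, 2 and 2. Splitting each cell equally gives 6 v 6 schools, 2:1 by authority and 1:1 by method in each arm. The correlation between arm and method is exactly 0, so omitting method does not bias the arm estimate.

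**2. Where does the taster effect go?** Let d be the difference between method B and method A schools that remains at T1 after adjustment for baseline MVPA. Six schools sit at +d/2 and six at −d/2, so the sum of squares is 12·d²/4. With intercept, arm and authority fitted, 12 − 3 = 9 school-level degrees of freedom remain, so omission adds (12·d²/4)/9 to the school-level mean square. With method fitted, 8 degrees of freedom remain and nothing is added.

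**3. Interval width.** Assumptions: total SD 1, ICC 0.05, 25 pupils analysed per school (the target is 30), t-based interval. Variance of a school mean: 0.05 + 0.95/25 = 0.088. Standard error of the arm difference: √(variance × (1/6 + 1/6)) = √(variance/3).

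Method included: 2.306 × √(0.088/3) = 0.395 SD, whatever d is.

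| d (SD) | Added variance | Half-width, method omitted | Omitted ÷ included |
|---|---|---|---|
| 0 | 0 | 2.262 × √(0.0880/3) = 0.387 | 0.98 |
| 0.10 | 0.0033 | 2.262 × √(0.0913/3) = 0.395 | 1.00 |
| 0.25 | 0.0208 | 2.262 × √(0.1088/3) = 0.431 | 1.09 |
| 0.40 | 0.0533 | 2.262 × √(0.1413/3) = 0.491 | 1.24 |

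Break-even is at about 0.10 SD. Below it the lost degree of freedom outweighs the gain, by at most about 2%.

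**4. ICC.** At d = 0.25 SD, the ICC from the model without method is (0.05 + 0.0208)/(0.05 + 0.0208 + 0.95) = 0.069. At d = 0.10 SD it is 0.0533/1.0033 = 0.053.

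**5. Minutes scale.** A REML mixed-model simulation (200 runs per value of d, normal-based intervals) assumed SD 15 min, ICC 0.03, 25 pupils per school and a true effect of 4 min.

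| d (min) | SE, omitted v included | ICC, omitted v included | Upper bound above 10 min, omitted v included |
|---|---|---|---|
| 0 | 2.26 v 2.26 | 0.032 v 0.032 | 29% v 30% |
| 2 | 2.36 v 2.30 | 0.037 v 0.034 | 30% v 27% |
| 4 | 2.58 v 2.24 | 0.052 v 0.031 | 42% v 28% |
| 6 | 3.01 v 2.26 | 0.082 v 0.032 | 50% v 23% |

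The mean arm estimate was the same with and without method at every d. The simulation concerns the overall effect, whereas the criterion uses boys and girls separately.

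**The case against.** The strongest reply is that allocation already does the work. The protocol says that taster effects "would be balanced between the two arms and can be separated from intervention effects", and for the point estimate that is correct. A reader might infer from the missing covariate that the taster contaminates the intervention effect, or that the promised separation fails. The documents do not support that: arm and method are orthogonal by design, and a taster-inflated baseline is inflated equally in both arms. What remains is a matter of precision, and the error is on the conservative side for the interval. This part of the reply stands.

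Second, the taster is a single 20–30 min session between the opt-out phase and baseline in May to July 2017, while T1 is the following February. Baseline MVPA is in the model and may absorb part of any effect. At an SD of 15 min, 0.25 SD is 3.75 min, close to the 4.3 min that the whole original programme achieved. The larger rows above are therefore illustrations, not expectations. This also stands, with one qualification. If the taster shifts baseline by s and the baseline slope is b, adjustment leaves about −b·s at T1 when the shift fades and (1 − b)·s when it persists. It cancels only if the persisting fraction equals b.

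Third, a reader might take the ICC change at 0.25 SD as a forecast of a larger definitive trial: with 30 pupils the design effect goes from 1 + 29 × 0.05 = 2.45 to 1 + 29 × 0.069 = 3.0, or 23% more children. That does not follow. Published ICCs are to be used as well, the article does not say that the ICC will come from this model, and an ICC from 12 schools is imprecise in any case (large-sample SE about 0.036 under these assumptions, against a shift of 0.02).

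Finally, with 12 schools a sparse model can be defended. That would explain leaving out both stratifiers better than it explains keeping one.

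**Conclusion.** The mismatch is real: allocation uses two stratifiers and the stated model adjusts for one, without a reason. The intervention estimate is unbiased (exactly so with equal numbers analysed per school, approximately so otherwise). If a taster effect survives baseline adjustment, the interval is too wide and a model-based ICC too high, and the upper-bound half of the fifth criterion becomes easier to pass. The criterion also requires an observed benefit, which this does not change.

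The size depends on assumptions that the documents cannot settle. With ICC 0.05 and 25 pupils per school, the interval is about 9% wider at 0.25 SD and unaffected near 0.1 SD. On the minutes scale, the change is small at 2 min and matters for the criterion only at about 4 to 6 min. The case for the change is that its cost is small and bounded, while the loss it guards against grows with the taster effect.

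**What to change.** Add recruitment method (A or B) as a fixed effect, beside local authority, in the main 12-school weekday MVPA model and in the boys' and girls' estimates used for the fifth progression criterion. Take any model-based ICC for the future sample size from that model. If the authors prefer to leave the term out, they should say why.

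The cost is one already recorded covariate and one of nine school-level degrees of freedom, about 2% of interval width (2.306/2.262 = 1.02) if the taster has no lasting effect.

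The change should not extend to the CACE analysis. Its four schools are all in South Gloucestershire, so local authority is constant. An intercept, arm and method would leave 4 − 3 = 1 school-level degree of freedom, and the article does not say that both recruitment methods occur among those schools.

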We recently completed an evaluation of the original Action 3:30 afterschool intervention [12]. The original feasibility study was conducted in 20 schools and participants were Year 5 and 6 pupils (9 to 11 year olds). Results showed that the Action 3:30 intervention could be implemented as planned, was liked by schools, children and TAs, and holds promise as a scalable physical activity approach [17, 18]. The adjusted difference in weekday MVPA at the end of the intervention was 4.3 min higher (95% CI = − 2.6 to 11.3) in the intervention arm. Exploratory, analyses indicated that the original intervention may hold more promise to increase boys’ activity (8.6 min, 95% CI = 2.8 to 14.5) than girls’ (0.15 min, 95% CI = − 9.7 to 10.0). The effect on mean levels of MVPA among boys is among the best that have been shown for physical activity interventions in children [19]. However, more work is needed to improve the content for girls, recruit less active participants, improve attendance and increase the TAs’ ability to manage disruptive behaviour [17, 18].

The aim of this study is to test the feasibility of the revised version of Action 3:30 which has been reworked to more successfully appeal to and engage girls and recruit less active children. Specifically, we have the following objectives:Objective 1: Optimise the intervention to increase activity in boys and girls.Objective 2: Identify effective means of recruiting low-active children.Objective 3: Assess intervention fidelity.Objective 4: Estimate the effect of allocation to the Action 3:30 intervention on weekday MVPA of participants and related physical activity behaviours.Objective 5: Collect the information needed to assess the feasibility of conducting a definitive trial and assess the implementation potential of the intervention.Objective 6: Assess whether progression criteria for conducting a definitive trial are met (see below).

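### The overall weekday MVPA model leaves out child sex, so a chance difference in sex mix between arms shifts the estimate slightly; adding sex is a small, free improvement

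*Protocol article*

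**What the plan says.** Under Quantitative analysis, the Protocol article names the covariates of the overall model: "random-effects linear regression models adjusting for intervention group, local authority, and baseline MVPA". Sex enters the plan only as a subgroup factor, in the continuation of that sentence: "with a focus on 95% confidence intervals with exploratory subgroup analyses by child gender".

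Under Recruitment it says: "As girls are less active than boys [21], we will aim for a minimum of 40% of the sample to be girls". That target is for the whole sample; no school-level quota is given. Each school contributes about 30 pupils, and oversubscription is settled by lot: "In schools where more than 30 children consent, 30 will be randomly selected for the study". No stratification of that draw by sex is stated.

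Under Allocation strategy: "Six schools will be randomly allocated into the intervention arm and six into the control arm, stratified by local authority area", and also by recruitment method. Sex mix is not a stratum.

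The fifth progression criterion, at the end of the Analysis plan, asks for a weekday MVPA benefit in boys and in girls separately.

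**The concern.** Sex is a baseline characteristic that the plan already uses for subgroups, and by the article's own statement it predicts the outcome. With only six schools per arm and no control of sex mix, the arms can differ in the share of girls. Baseline MVPA carries part of the sex difference, but T0 is in May to July and T1 the following February, so the correlation between them is unlikely to be close to one. What baseline MVPA leaves over stays in the overall Objective 4 estimate when the arms are unbalanced, and otherwise remains as residual variation that could have been removed.

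**Working it through.** **Inputs from the Protocol article.** Twelve schools, six per arm; about 30 pupils per school. Earlier study: "4.3 min higher (95% CI = − 2.6 to 11.3) in the intervention arm". The article gives no SD, sex gap, baseline to follow-up correlation or ICC, so there is no planned figure to reproduce.

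**Assumed inputs.** For the shift: within-sex SD 18 min (variance 324), sex gap g of 8 to 15 min at both time points, within-sex T0 to T1 correlation r of 0.4 to 0.6, about half girls. For the chance imbalance: 45% girls and a between-school SD of the share of girls of 0 to 0.20.

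**1. Yardstick.** SE of the earlier estimate = (11.3 + 2.6) / 2 / 1.96 = 6.95 / 1.96 = 3.55 min.

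**2. Shift for a 10-point difference in the share of girls.** Without sex in the model, the slope on baseline MVPA is b = (324r + g²/4) / (324 + g²/4), and the shift is (1 − b) × g × 0.10.

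- g = 8, r = 0.6: b = (194.4 + 16) / 340 = 0.619; shift = 0.381 × 8 × 0.10 = 0.30 min.
- g = 15, r = 0.4: b = (129.6 + 56.25) / 380.25 = 0.489; shift = 0.511 × 15 × 0.10 = 0.77 min.

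Against 3.55 min this is about 0.1 to 0.2 of a standard error. The simpler approximation g × (1 − r) × 0.10, with the gap widened to 5 to 15 min, gives 0.2 to 0.9 min.

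**3. How likely a 10-point difference is.** SD of the between-arm difference = √(2v/6), with v = 0.45 × 0.55 / 30 + s², where s is the between-school SD of the share of girls.

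| s | v | SD of difference | 10 points in SDs |
|---|---|---|---|
| 0 | 0.00825 | 0.052 | 1.9 |
| 0.10 | 0.01825 | 0.078 | 1.3 |
| 0.20 | 0.04825 | 0.127 | 0.8 |

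**4. Child-level residual variance.** With sex it is 324(1 − r²); without sex it is (324 + g²/4)(1 − b²).

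- g = 8, r = 0.6: 207.4 against 209.8, a reduction of 1.2%.
- g = 15, r = 0.4: 272.2 against 289.4, a reduction of 6.0%.

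**5. Precision of the arm estimate.** This is what matters, and it gains less than the child-level variance does. In a simulation of 12 schools with 27 analysed pupils each, SD 20, ICC 0.05 and no true effect, the SD of the estimate without and with sex was:

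- gap 5, correlation 0.4, s = 0.10: 3.30 and 3.29 min;
- gap 10, correlation 0.4, s = 0.10: 3.33 and 3.29 min;
- gap 15, correlation 0.4, s = 0.20: 3.49 and 3.37 min.

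The gain is about 0 to 4%. Both models averaged within 0.1 min of zero. As a cross-check at the extreme, the shift has SD 7.67 × 0.127 = 0.97 min, and √(3.55² − 0.97²) = 3.41, a reduction of 3.8%.

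**6. ICC.** Take g = 15, r = 0.4 and a sex-adjusted ICC of 0.050, so the between-school variance is 0.050 × 272.2 = 13.6. Leaving sex out adds (7.67s)² to it and raises the total to 289.4.

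- s = 0.10: (13.6 + 0.6) / 289.4 = 0.049.
- s = 0.20: (13.6 + 2.4) / 289.4 = 0.055.

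Even at the large end of the assumed gap the change is very small, and it need not be upward.

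**The case against.** The strongest reply is that leaving a predictor out of a randomised comparison is valid, contradicts nothing in the article, and that the SAP, not shown here, may add sex. Validity is conceded. But the article does state a covariate list, and that list omits a predictor which the article itself names, so this is a choice that can be improved and not a detail left open.

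A reader might infer that the overall estimate is biased. It is not: schools are randomised, imbalance arises by chance, and the confidence interval already reflects that variation. A reader might also suppose that re-enrolment, which is planned only in intervention schools, or loss of accelerometer data would make the imbalance systematic. Nothing in the article shows that either would differ by sex between arms.

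It can also be said that sex is handled where the decision is taken. That stands for the progression criterion: a comparison within boys or within girls cannot be moved by the sex mix. It does not help the overall estimate, which the subgroup analyses leave unadjusted.

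Setting the shift against the earlier 4.3 min effect (0.30 / 4.3 = 7%; 0.77 / 4.3 = 18%) makes it look larger than it is. The uncertainty of that effect is the fairer scale.

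**Conclusion.** The point holds as a minor improvement to the overall Objective 4 estimate. A 10-point difference in the share of girls would move the estimate by about 0.3 to 0.8 min, and adjustment would improve precision by roughly 0 to 4%. Both figures rest on the assumed SD, sex gap, correlation and between-school variation; a sex gap that widened between T0 and T1 would leave more unadjusted than shown.

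Three stronger conclusions are not supported: that the estimate is biased, that the progression decision is affected, or that the ICC for the definitive trial is materially distorted. The article does not say which model will supply the ICC, and it will be used together with published values. Nor does the article give grounds for adding school year on the same reasoning, since it reports no activity difference between the two adjacent years enrolled.

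**What to change.** Pre-specify child sex as a fixed effect in the overall weekday MVPA model, alongside arm, local authority and baseline MVPA. Keep the sex-specific analyses as planned. If the ICC is taken from this model, report it with the covariate set used, so that it is matched to the model intended for the definitive trial.

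The cost is one model term and one child-level degree of freedom. No new measurement is needed, because the plan already analyses by sex. Fixing the term in advance also avoids having to decide on it after an imbalance has been seen.
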